#### Analysis

In this randomized controlled trial, equivalence tests for two proportions in a cluster-randomized design will be performed according to requirements in the CONSORT (Consolidated Standards of Reporting Trials) statement. Sociodemographic, clinical, and economic data will be analyzed per group.

Baseline characteristics at enrollment will be reported as the mean and standard deviation (SD) for continuous variables and percentage for categorical variables. Continuous variables not normally distributed will also be presented as a median and interquartile range.

Missing data will be imputed using multiple imputation regression methods.

Cox analysis will be used to compare all-cause mortality, acute nonfatal cerebro-cardiovascular events, and hospitalization before and after dialysis treatment between the two groups.

T-tests will be performed to compare nutritional status, quality of life, residual renal function (urine volume), and medical expenses based on a data-paired analysis (before-after study). Continuous data will be compared using a paired t-test if the variable is normally distributed or Wilcoxon test for non-parametric variables. The MacNemar test will be used for categorical variables (Fleiss test, if necessary).

Statistical significance will be considered at a value of *p* ≤ 0.05. All statistical analyses will be performed with SAS, version 9.4 (SAS Institute, Cary, NC; USA).

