### Trial intervention and visit schedule

#### Randomization

Cluster randomization was utilized. The intervention was applied at the facility level to avoid the possibility of experimental contamination at the patient level. Sixteen tertiary hospitals across China have been randomly assigned to the routine and deferred dialysis groups using a random number generator. At each site, on referral to the study, participants will be sequentially allocated a unique identifying number to be used for all subsequent study documentation. This will ensure confidentiality is maintained.

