### Statistical analysis

#### Sample size

In this study, a cluster randomized design is used. The primary endpoint of the study is death rate, which will be determined by survival analysis. According to the IDEAL study, the death rate was 37% during a median follow-up period of 3.59 years [9]. Because we include relatively stable patients the mortality rate may be lower; we assume the death rate will be 30% or less within 3 years. The project selection window for patient enrollment is 30 months. Sood et al. found an adjusted facility-level intraclass correlation coefficient (ICC) of 0.031 in their work [16]. We get 8 clusters per group. Scholars have proposed that a sample size calculated assuming individual randomization can be inflated by a Design Effect (DE) to reach the required level of statistical power under cluster randomization [17]: DE = 1+ (m-1) ρ, where m is the number of individuals per cluster and ρ is the ICC.

If we assume that alpha = 5%, (1-beta) = 80%, patients are assigned 1:1, a difference of 10% in death rates between these two groups is considered acceptable. We use log-rank tests to get the events (87 vs 57) with the Power Analysis and Sample Size Software, version 13 (NCSS, LLC. Kaysville, Utah, USA) and the number of individuals per group is 473. Thus, the number of total events under the consideration of cluster effects is 198 (128 vs 70). This is an endpoint driven study. We will complete the study when we get enough endpoint events, which is 198 events.

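### The Cox comparison of the arms is given without any allowance for the 16 randomised hospitals; run that way, its nominal 5% test would have a true size of about 18–24% at the plan's own ICC

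*Protocol article*

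**What the plan says.** **Randomization.** The hospital is the unit: "Sixteen tertiary hospitals across China have been randomly assigned to the routine and deferred dialysis groups using a random number generator".

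**Sample size.** The section plans for a cluster design. It states "We get 8 clusters per group", takes an "adjusted facility-level intraclass correlation coefficient (ICC) of 0.031" from an outside study, and gives DE = 1 + (m − 1)ρ, "where m is the number of individuals per cluster and ρ is the ICC". It reports that "the number of individuals per group is 473". It names death rate, assessed by survival analysis, as the primary endpoint. The trial is sized on log-rank events: 144 (87 + 57), raised to 198 (128 + 70) for clustering.

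**Analysis.** The section opens with an equivalence test of two proportions, the only method described as being for a cluster-randomised design. It continues: "Cox analysis will be used to compare all-cause mortality, acute nonfatal cerebro-cardiovascular events, and hospitalization" between the groups. No frailty term, robust variance, hospital effect or degrees of freedom is mentioned. For other outcomes, "T-tests will be performed to compare nutritional status, quality of life, residual renal function (urine volume" and costs are analysed as paired before-after data, with Wilcoxon and McNemar tests as the alternatives. One threshold, p ≤ 0.05, covers everything.

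**The concern.** Patients in one hospital share its staff, case mix and practice, and all of them are in the same arm. A standard Cox model counts each patient as independent information about the treatment effect, so its standard error leaves out the between-hospital variation. The plan accepts that this variation exists when it sets the number of events, but does not carry it into the comparison those events are meant to serve.

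The stake is the survival result. An unadjusted hazard ratio would have too narrow an interval and too small a p-value. If the aim is equivalence, as the Analysis section also says, an interval that is too narrow makes a false conclusion of equivalence easier to reach.

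**Working it through.** **Inputs.** All from the Sample size section unless marked: 8 hospitals per arm; 473 patients per arm; ICC 0.031; alpha 5%; power 80%; 30% deaths at 3 years; a 10-point difference. A two-sided test is assumed, because the sidedness is not stated.

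**1. Reproduce the plan's events.** Reading the difference as 30% vs 20%, HR = ln 0.8 / ln 0.7 = 0.626. Schoenfeld: 4(1.960 + 0.842)² / (ln 0.626)² = 143 events, against 144 stated. A one-sided test would need 113. The starting figure is therefore a two-sided log-rank calculation for independent patients.

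**2. Design effect.** m = 473/8 = 59.1. DE = 1 + 58.1 × 0.031 = 2.80; √DE = 1.67.

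**3. True size of an unadjusted 5% test.** 2[1 − Φ(1.96/1.67)] = 2[1 − Φ(1.17)] = 24.2%.

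**4. Interval width.** On the normal scale an unadjusted interval is 1/1.67 = 0.60 of the proper width. With 16 hospitals in two arms, a t reference on 14 df is appropriate. Its 97.5% point is 2.145, so the proper interval is 1.67 × 2.145/1.96 = 1.83 times the unadjusted one, and 1/1.83 = 0.55.

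**5. Simulation.** The formula in step 2 is for proportions, so it was checked on an unadjusted log-rank test, which is the Cox score test. Settings: 8 + 8 hospitals, 59 patients each, shared gamma frailty set to give ICC 0.031 for 3-year death, no treatment effect, 4,000 runs each.

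| Follow-up | 25% risk | 21% risk |
|---|---|---|
| Full 3 years | 24.6% | 24.5% |
| Staggered: censoring uniform from 0.6 to 3 years (assumption) | 18.0% | 18.4% |

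**6. Dependence on the inputs** (formula of step 3):

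| Setting | DE | True size |
|---|---|---|
| ICC 0.005, m = 59 | 1.29 | 8.5% |
| ICC 0.01, m = 59 | 1.58 | 11.9% |
| ICC 0.02, m = 59 | 2.16 | 18.3% |
| ICC 0.031, m = 59 | 2.80 | 24.2% |
| ICC 0.05, m = 59 | 3.91 | 32.1% |
| ICC 0.031, m = 36 (87/0.30 = 290 per arm, before inflation) | 2.09 | 17.5% |
| Inflation the plan applied to events, 198/144 | 1.375 | 9.5% |

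None of these settings brings the size back to 5%.

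**7. Power once adjusted.** 198/2.80 = 71 effective events. Power at HR 0.626 = Φ(0.469 × √71 / 2 − 1.96) ≈ 50%, by normal approximation.

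**The case against.** The strongest reply is that the Analysis section is silent rather than wrong. A condensed article may leave frailty terms, robust variance and degrees of freedom to the full protocol or an analysis plan. The visible text also shows awareness of clustering, in the sample size and in the proportions test. This stands in part: a reader might infer that the trial has chosen to analyse patients as independent, and the article does not say so. It does not dispose of the point. The section does address the cluster design, but attaches it to one method and leaves it off the survival comparison on which the trial was sized.

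Three limits on the figure also stand:

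- **Paired tests.** A reader might carry the 24% over to the t-test, Wilcoxon and McNemar tests. The article describes these as before-after comparisons within patients, whereas the 24% is for a between-arm test. No ICC is given for those outcomes. The main weakness of those tests is a different one: they do not compare the arms.
- **Conditions.** The ICC comes from an outside study, and the article does not say which outcome it concerns. Enrolment over 30 months with event-driven closure means staggered follow-up, so the 24% for full follow-up is not the only plausible value.
- **Which error.** The 24% is the false-positive rate of a test for a difference. It is not the error rate of the equivalence test, which is described as suited to the cluster design.

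**Conclusion.** The point holds in conditional form. As written, the Cox analysis of mortality, nonfatal events and hospitalisation makes no allowance for the randomised hospitals. If it is run that way, a two-sided 5% between-arm test has a true size of about 24% with full follow-up and about 18% under the assumed staggered censoring. Both figures take the plan's ICC of 0.031 and 59 patients per hospital, and the calculated range is 8.5% to 32% for an ICC of 0.005 to 0.05. Intervals would be 0.55 to 0.60 of the proper width. The documents do not show a decision to ignore clustering, and they support no such figure for the paired tests. The matter should be settled before analysis, because a choice made later between narrow and valid intervals would be open to question.

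**What to change.** In the Analysis section, state that:

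- the Cox analysis accounts for hospital, by robust variance with a small-sample correction or by shared frailty, with inference suited to 16 clusters (t on 14 df);
- a cluster-level comparison of hospital event rates supports it;
- any between-arm comparison of secondary outcomes includes a hospital effect.

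The work is a few sentences and routine SAS code, with no change to recruitment or treatment. The cost is in precision: intervals about 1.8 times wider than unadjusted ones, and power at 198 events below the stated 80%. The sample size section should restate that power. It is about 50% at HR 0.626 and ICC 0.031 by normal approximation, and somewhat less with the t reference.

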#### Secondary endpoints

The secondary outcomes will allow the investigators to:
Assess the hospitalization rates by comparing proportion of patients who are admitted to hospital before and after dialysis treatment between the two groups;Assess the nutritional status before and after dialysis treatment between the two groups by using SGA assessment and serum albumin levels;Assess patient reported quality of life by using SF-36.Assess the complications of dialysis after dialysis treatment between the two groups;Implement a cost study.•Assess arteriovenous fistulas rate and catheter usage as blood access at first dialysis.

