### Economic evaluation

#### Cost measurement

To assess the total cost of each group, the number of resources consumed will be prospectively collected for each patient (drugs, medical devices, consultations, hospitalization, etc.). The receipts from each visit will be used to record the patient’s costs during the follow-up period.

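### Nutrition, quality of life, urine volume and cost are assigned only paired before-after tests, which do not compare routine with deferred dialysis

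*Protocol article*

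**What the plan says.** The Secondary endpoints section of the protocol article sets the nutrition aim as "Assess the nutritional status before and after dialysis treatment between the two groups by using SGA assessment and serum albumin levels". For cost, the Cost measurement section gives the purpose: "To assess the total cost of each group, the number of resources consumed will be prospectively collected for each patient". The quality-of-life item says only that SF-36 will be used. Urine volume is not listed as a secondary endpoint.

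The Analysis section then names the tests. For time-to-event outcomes, "Cox analysis will be used to compare all-cause mortality, acute nonfatal cerebro-cardiovascular events, and hospitalization before and after dialysis treatment between the two groups". For four further outcomes it describes a paired, before-after analysis: "T-tests will be performed to compare nutritional status, quality of life, residual renal function (urine volume), and medical expenses based on a data-paired analysis". It adds: "Continuous data will be compared using a paired t-test if the variable is normally distributed or Wilcoxon test for non-parametric variables". And "The MacNemar test will be used for categorical variables". The same section plans multiple imputation for missing data and says that sociodemographic, clinical and economic data are analysed by group.

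**The concern.** A paired test asks whether patients differ after an event from before it. The trial asks whether patients at hospitals assigned to defer dialysis fare differently from patients at hospitals following routine timing. A significant paired result in one group, in both, or in the groups combined does not answer that question.

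The Discussion relies on randomization to overcome selection bias and confounding. Followed as written, the plan gives up that advantage for nutrition, quality of life and cost. These outcomes would carry much of any argument that deferral is tolerable and saves money.

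**Working it through.** **Aim against test**

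- Nutrition: the aim is a comparison between the two groups. The test is paired t or Wilcoxon for albumin and McNemar for categorical SGA. They do not match.
- Cost: the aim is the total cost of each group. The test is a paired comparison of expenses. Any saving from deferral would arise from time spent off dialysis. A before-after comparison mainly shows how spending changes once dialysis starts, in either group.
- Quality of life: no contrast is stated in the aim, and the only test is paired.
- Hospitalization: the aim and the Cox analysis are both between groups. They match.

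**The anchor**

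The Analysis section says only before-after. The endpoint wording makes before and after dialysis the natural reading. The intervention changes when dialysis starts, so pairing around that start conditions on an event after randomization. SGA grade C is also one of the listed indications for starting dialysis, and Table 4 schedules SGA at initiation. For patients who start on that indication, a before value taken at initiation is selected to be low, and regression to the mean can look like improvement.

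**Size of the misleading signal (illustration)**

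Inputs from the article: 473 patients per group, 8 hospitals per group, ICC 0.031, significance at 0.05. Applying that ICC to these outcomes is an assumption. Also assumed: a true before-after change of 0.1 or 0.2 SD (SD of the change), identical in both groups, so the true group difference is zero.

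The noncentrality of a paired t-test is d × √n. With d = 0.1 and n = 473 it is 0.1 × 21.75 = 2.17, which gives power 0.583. Two separate tests disagree with probability 2 × 0.583 × (1 − 0.583) = 0.486. Pooled, n = 946 and the noncentrality is 0.1 × 30.76 = 3.08, which gives power 0.867. The clustered row comes from 4,000 simulated trials per setting.

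| Setting | Pooled paired test significant (0.1 / 0.2 SD) | One group significant, the other not (0.1 / 0.2 SD) |
|---|---|---|
| 473 independent pairs per group | 87% / over 99% | 49% / 2% |
| 237 independent pairs per group | 58% / 99% | 45% / 23% |
| 8 hospitals × 59 pairs per group, ICC 0.031 | 75% / 99% | 48% / 14% |

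**What a repair needs**

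In the clustered setting with 59 pairs per hospital, an unadjusted two-sample t-test rejects a true null in about 24% of trials. This agrees with theory: the design effect is 1 + 58 × 0.031 = 2.80, its square root is 1.67, and 2 × [1 − Φ(1.96/1.67)] is about 0.24. A t-test on hospital means rejects in about 5%. Comparing the groups is therefore not enough; the hospital must be accounted for.

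**The case against.** **The article condenses a fuller plan.** That would excuse silence. Here the article names specific tests, and they do not answer its own stated aims.

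**Analysis by group, or the opening sentence of the Analysis section, may supply the comparison.** Separate paired tests in each group are not a test between groups, as the disagreement rates show. The opening sentence does promise equivalence tests for two proportions in a cluster-randomized design. It is tied to no outcome, cannot serve for SF-36 scores, albumin or cost, and fits the primary endpoint, which is defined by proportions.

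**Several stronger readings are tempting, and the article does not support them.**

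- A reader might infer that all secondary outcomes lack a group comparison. Hospitalization has one. Dialysis complications and vascular access at first dialysis are not on the paired list.
- A reader might infer that everyone who dies before dialysis or never starts is excluded. No exclusion rule is stated, and multiple imputation is planned. What stands is that these patients have no observable later value, and that an imputed post-dialysis value for someone who died before dialysis is hard to interpret.
- A reader might want to put a figure on that loss. At 30% mortality over 3 years the hazard is −ln(0.7)/3 = 0.1189 per year. Assumed starts at 6 versus 9 months give 5.8% versus 8.5% dead before dialysis; 12 versus 20 months give 11.2% versus 18.0%. The article gives neither start times nor the proportion expected to start, and 30% is its upper value. No figure can be defended.
- A reader might infer that the urine-volume pair cannot be formed. Table 4 schedules urine output at initiation and afterwards, so the initiation value can serve as the earlier one.

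**Conclusion.** The point holds for nutritional status, quality of life, urine volume and medical expenses. The only tests named for them estimate within-patient change. The contradiction with a stated aim is direct for nutrition and implied for cost. For quality of life the aim names no contrast, but the plan still yields no randomized comparison. The primary endpoint and hospitalization are not affected by this point.

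The mismatch itself rests on the text alone and needs no assumption. The percentages illustrate its effect and depend on the assumed 0.1 to 0.2 SD change and, in the clustered setting, on the borrowed ICC. How patients without a post-dialysis value are handled is unstated; that is a gap, not a declared exclusion.

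**What to change.** Reword the Analysis section, and the statistical analysis plan if it follows the same lines:

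1. Make the main analysis of SF-36, SGA grade, albumin and cumulative cost a comparison between groups at fixed times from inclusion, in all enrolled patients. Adjust for the baseline value where one is recorded. Table 4 has an inclusion value for SF-36, SGA and albumin, but not for cost.
2. Account for hospital, either with a mixed model or GEE that has a small-sample correction suited to 8 hospitals per group, or with hospital-level summaries. A bootstrap over 8 hospitals per group is fragile and should not be the sole basis for the cost interval.
3. State for each outcome how death is handled. A mixed model does not settle this by itself.
4. Keep before-after changes as descriptive.
5. Describe urine volume from dialysis initiation onward, and do not present it as a randomized comparison.

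Table 4 already schedules SF-36 and SGA every six months, and albumin and cost quarterly, before and after dialysis. If the post-dialysis visits are counted afresh from initiation, which the article does not say, visit windows from inclusion will be needed. The cost is rewording and some added analysis work, with no new data collection.

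### Medical expenses fall under a switch to the Wilcoxon test when not normal; as written this tests symmetry of before-after differences, not mean cost, although the economic aim is total cost per group

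*Protocol article*

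**What the plan says.** Under Secondary endpoints the protocol article lists "Implement a cost study". Under Cost measurement it gives the purpose: "To assess the total cost of each group, the number of resources consumed will be prospectively collected for each patient". The resources named there include drugs, devices, consultations and hospitalization.

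Under Analysis it states: "T-tests will be performed to compare nutritional status, quality of life, residual renal function (urine volume), and medical expenses". The same sentence makes this a paired, before-after comparison. The next sentence sets the choice of test for every continuous variable: "Continuous data will be compared using a paired t-test if the variable is normally distributed or Wilcoxon test for non-parametric variables". Costs are not exempted, and no separate comparison of mean costs is named.

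**The concern.** A total is a mean multiplied by a head count, so a question about the total cost of a group is answered by arithmetic means. The rule in the Analysis section moves away from means as soon as a variable is judged non-normal. Per-patient expenses cannot be negative, and a few long admissions usually give them a long right tail, so this variable is a likely candidate for the switch.

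The Wilcoxon test is offered as the alternative to a paired t-test, so it is the signed-rank test on within-patient differences. Its null is symmetry of those differences about zero. That matches equal mean cost only if the differences are symmetric. Starting dialysis may well change the spread and tail of a patient's costs as well as their level. The test can then be significant when mean cost has not changed. It can also miss a rise that comes from a few very expensive patients, who add heavily to the total but count only by rank. The economic burden of dialysis is part of the trial's rationale in the Background, so the cost result will be read with interest.

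**Working it through.** The protocol states no cost figure to reproduce. The check is whether the test's null matches the target and, if not, how far apart they can be.

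**Inputs from the protocol article**
- Test rule and paired design: Analysis section.
- Target: total cost of each group, Cost measurement section.
- Significance level 0.05: Analysis section. Two-sided is assumed.
- Group size: "the number of individuals per group is 473" (Sample size section). Before-after pairs exist only for patients who start dialysis, so 473 is an upper bound on pairs per group. Smaller numbers (100, 300) are shown beside it.

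**Assumptions, because no cost distribution is given:** lognormal costs, log-scale SDs as listed, log-scale correlation 0.4 between a patient's before and after costs, no clustering.

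**Why the two quantities separate.** For a lognormal cost with log-mean μ and log-SD σ, the mean is exp(μ + σ²/2) and the median is exp(μ). With equal means before (σ = 0.8) and after (σ = 1.0), the after/before ratio of medians is exp((0.8² − 1.0²)/2) = exp(−0.18) = 0.84. Total spending is unchanged, yet the typical patient's bill is about 16% lower, and a rank test responds to that. Conversely, with equal medians and σ = 0.8 vs 1.04, the ratio of means is exp((1.04² − 0.8²)/2) = exp(0.2208) = 1.25. Total spending is 25% higher with no change in the median.

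**Simulated rejection rates at nominal 5%**

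| Scenario | Pairs | Signed-rank | Paired t |
|---|---|---|---|
| Equal means, 0.8 vs 1.0 | 100 | 17% | about 4–6% |
| Equal means, 0.8 vs 1.0 | 300 | 44% | about 4–6% |
| Equal means, 0.8 vs 1.0 | 473 | 63% | about 4–6% |
| Equal means, same shape, 0.8 vs 0.8 | 100 to 473 | about 5% | about 5% |
| Mean 25% higher, equal median, 0.8 vs 1.04 | 473 | 33% | 93% |
| Mean ratio 1.5, 0.8 vs 1.0 | 300, 473 | at least 99% | at least 99% |

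**Sensitivity.** With correlation 0.3 and equal means, the signed-rank test rejects as follows:
- 0.8 vs 1.0: 16%, 30% and 58% at 100, 200 and 473 pairs.
- 0.6 vs 1.0: 45%, 73% and 98%.
- 0.5 vs 1.2: 83%, 98% and 100%.

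The paired t-test stays between 4.8% and 6.8% at 473 pairs, but reaches 10.6% at 100 pairs with 0.5 vs 1.2. A bare t-test is therefore not fully safe under strong skew with few pairs.

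**The case against.** Four counter-arguments deserve weight.

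First, the phrase about total cost stands under Cost measurement and explains why resources are recorded. Group totals and means can be reported whatever test is run on paired differences. That is true, but no other test is named for expenses, so the significance statement for the cost study would rest on this rule.

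Second, equal mean cost before and after dialysis starts is an unlikely state, since the Background describes dialysis as a heavy burden. This stands in part: with a mean ratio of 1.5 and 300 or more pairs, both tests reject almost always. The conflict is confined to small or moderate changes in the mean.

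Third, the sizes are assumed. They are; the distribution, the spreads, the correlation and the number of pairs are not in the document, and normality may be judged in a way that keeps the t-test. What does not depend on these assumptions is that the signed-rank null differs from equal means.

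Fourth, the before-after test does not compare the arms at all, which is a larger gap relative to the stated aim. This stands. A reader might infer that the rule could make deferral look cheaper when spending is equal or higher. The document does not support that: it names no between-arm cost test, so rank-sum error rates describe a comparison that it does not plan. That conclusion would arise only if the same normality switch were carried over to a between-arm cost comparison.

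**Conclusion.** The point holds in a limited form. The protocol states a test-selection rule that covers medical expenses and, on its likely branch, tests something other than mean cost. This does not match the aim of assessing total cost per group. It is a stated choice, not a detail left to a later plan.

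The size is conditional. Under the lognormal assumptions above, false rejection with equal means runs from about 17% (100 pairs) to 63% (473 pairs, the ceiling), and a 25% tail-driven rise is found 33% instead of 93% of the time at that ceiling. With matching shapes there is no inflation. Only a secondary outcome is affected; the primary endpoint and the sample size are not. The change is worth making because it is cheap.

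**What to change.** Exempt medical expenses from the normality switch. State that arithmetic mean cost per patient will be compared between the two groups whatever its distribution, with a 95% confidence interval that respects hospital clustering and is corrected for 8 hospitals per arm. Two suitable forms are:
- a t-based analysis of hospital mean costs, with 16 − 2 = 14 degrees of freedom;
- a gamma model with log link and small-sample-corrected hospital-robust errors.

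An uncorrected percentile bootstrap of hospitals is not suitable: with 8 hospitals per arm, simulations under assumed lognormal costs put its error at about 8–10% at nominal 5%. Medians and any Wilcoxon result can be given as description only.

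The cost is a short rewrite of the Analysis section and some programming, with no new data. It is more than a change of test, because it also replaces the before-after comparison of expenses with a between-arm one. The downside is a wider interval that is sensitive to a few extreme bills.
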